| Compliance assessment                                                                     |                        |                            | X        | X         | X          | X                            |
| Adverse Event
Monitoring                                                               |                        | X                          | X        | X         | X          | X                            |
| Investigational product
supply                                                         |                        | X                          | X        | X         |            |                              |
| Study drug administration                                                                 |                        | Day 1 – Day 180±14 days    |          |           |            |                              |

 Informed Consent Form must be obtained prior to performing any study-related procedures;  
 Body weight and height will be obtained without outerwear and shoes; BMI = weight (kg)/height (m^2)

 Subjects will be randomized just prior to dosing. Further drug intake will be done according to the randomization scheme.

\* Not necessary if complete information was obtained upon Screening

\*\* Not necessary if screening (visit 1) and randomization (visit 2) are performed on the same day (which will be Day 1).

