### 5.4 Subject Withdrawal Criteria

1. The patient withdraws the Informed Consent.

2. Patient's pregnancy: patients will be recommended to use effective contraception methods during the study, however if pregnancy occurs during the study, the IP/placebo treatment and other study procedures concerning the pregnant patient are cancelled, patient's pregnancy will be monitored up to pregnancy completion if the patient agrees.
3. Any medical condition of the patient that requires withdrawal of that patient from the study, as judged by the Investigator.
4. Patient lost to follow-up.

The investigator can withdraw a subject from the study if any of the withdrawal criteria are met. Patients are free to withdraw from the study at any time upon request, without any consequence. Patients should be listed as having withdrawn consent only when they no longer wish to participate in the study and no longer authorize the investigators to make efforts to continue collection of the outcomes. Every effort should be made to encourage patients to remain in the study for the duration of the planned outcome assessments. The patients should be told that their data are important for the scientific research, even after they discontinue the drug product.

The participant should no longer be contacted regarding the study after notification of withdrawal.

A subject will be considered lost to follow-up if he or she fails to appear for a follow-up assessment and cannot be contacted with good effort. These efforts will be documented in the subject's record. If not a single dose of the IP/comparator was taken by the patient, and he/she left the study for any reason, then further follow-up is cancelled, and his/her data are not included in the statistical analysis.

If the patient decides to leave the study or does not complete the study for any reason, then his randomization code should not be reused.

Unless the patient withdraws consent, those who discontinue the IP early remain in the study, if possible, for further collection of outcomes. The reason for discontinuation of the IP should be documented in the CRF.

The Investigator submits the data on the withdrawn patients to the Sponsor, local Principal Investigator and the monitor of the study within 24 hours in a report that includes the patient's status at the end of the study, as follows:

1. *Completed the study.*
2. *Did not complete the study because of:*

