#### 9.1.2 Efficacy analysis

Primary analysis will employ ITT population, sensitivity analyses will be performed using ITT population with LOCF imputations and PP population.

Primary efficacy endpoint: Change in complex attention score, determined using Central Nervous System Vital Signs (CNS-VS) computer cognitive testing system, after 6 months of treatment compared to baseline in the group of patients receiving NeuroAiD II™ (MLC901), compared to the placebo group.

For primary endpoint analysis for each patient, the difference in complex attention scores, determined using CNS-VS computer testing, after 6 months of therapy compared to baseline, will be calculated: the change in complex attention score compared to baseline. Mixed effects model (PROC MIXED) will be used with adjustments for baseline and potential covariates. All timepoints will be used for the model. The participant and site will be used as the random effects. Model selection will be undertaken with each outcome using standard selection heuristics. Covariates will be selected based on improving the overall efficiency of the model. Regardless, baseline and age, gender, time since injury (1-3 months/4-12 months) and study center will be included as covariates in the mixed effects model. Descriptive statistics will be calculated to change in complex attention in each group, as well as mean values obtained by the method of least squares from the mixed effects model.

Superiority of MLC901 over placebo will be claimed if

$H_0: \text{LSM}_T \geq \text{LSM}_R$  is rejected and thereafter

$H_1: \text{LSM}_T < \text{LSM}_R$  is accepted at significance level of 5%,

where  $\text{LSM}_T$  is a Least Square Mean of Change from Baseline of Complex attention score after 6 months of treatment assessed by the mixed model repeated measures analysis in the MLC901 group and  $\text{LSM}_R$  is a Least Square Mean of Change from Baseline of Complex attention score

after 6 months of treatment assessed by the mixed model repeated measures analysis in the Placebo group (lower score of Complex attention is better).

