### **9.7 Selection of Subjects to be Included in the Analyses**

Following populations will be analyzed:

1. Intention-to-treat population (ITT), which includes every subject who is randomized according to randomized treatment assignment.
2. Per-Protocol population (PP): includes all subjects from ITT population who complete all assessments needed for primary endpoint calculation except subjects with significant protocol deviations.
3. Safety population: Patients who received at least one IP/Placebo dose, according to the prescribed treatment.

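### Section 5.4 removes randomized patients who take no dose and then leave the study, although section 9.7 keeps every randomized patient in the primary ITT set

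*Protocol*

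**What the plan says.** Section 9.7 of the protocol defines the primary set as the "Intention-to-treat population (ITT), which includes every subject who is randomized according to randomized treatment assignment". No dose is required. A dose condition appears in that section only for the third set: "Safety population: Patients who received at least one IP/Placebo dose, according to the prescribed treatment". Section 9.1.2 then states: "Primary analysis will employ ITT population, sensitivity analyses will be performed using ITT population with LOCF imputations and PP population".

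Section 5.4 sets a different rule. It has two conditions, that the patient never took any study product and that the patient has left, whatever the cause. Where both are met, the instruction reads: "then further follow-up is cancelled, and his/her data are not included in the statistical analysis". It makes no exception for ITT and does not restrict itself to patients who were never randomized. The same section takes the opposite line for patients who have started treatment: "Unless the patient withdraws consent, those who discontinue the IP early remain in the study, if possible, for further collection of outcomes".

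Two other places matter. A footnote to the schedule in section 1.3 says: "Subjects will be randomized just prior to dosing". Section 4.1 and the synopsis require an Early-Termination visit for any patient who leaves before completion, whatever the cause. That visit carries the End-of-Study assessments, which include CNS-VS.

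**The concern.** An ITT set that admits every randomized subject cannot also exclude some of them after randomization. If the exclusion in 5.4 is applied, the primary set is really a modified ITT (randomized, and either dosed or still in the study) under the ITT label. Two analysts working from the same protocol could report different ITT counts.

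The ITT-LOCF sensitivity set could differ as well. Baseline CNS-VS is taken at Visit 2, so an undosed leaver may have a baseline value that enters under 9.7 and is removed under 5.4.

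Cancelling follow-up matters more in practice, because an analysis plan cannot repair it. A later decision to honour 9.7 can restore a patient to the count, but not an outcome that the site did not collect.

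**Working it through.** This is a conflict of definitions, so the main check is to run each type of patient through the rules.

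| Patient | Section 9.7 (ITT) | Section 5.4 | Conflict? |
|---|---|---|---|
| Screened, never randomized, leaves | Not in ITT | Excluded, follow-up cancelled | No |
| Randomized, no dose, stays in study | In ITT | Rule not triggered | No |
| Randomized, no dose, leaves; consent to outcome collection remains | In ITT | Excluded, follow-up cancelled | Yes: analysis set, and the visit required by 4.1 |
| Randomized, no dose, withdraws consent or cannot be reached | In ITT | Excluded, follow-up cancelled | Yes: analysis set; little or no outcome obtainable |
| Randomized, dosed, stops product early | In ITT | Kept for outcomes unless consent is withdrawn | No |

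The third and fourth rows can occur because randomization precedes dosing. Nothing in 5.4 confines its rule to the first row.

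**The plan's own sample size.** Inputs from section 9.2: difference 10, SD 20, two-sided alpha 0.05, power 80%, 1:1 allocation, 30% dropout. A two-sample t-test needs 63.8, so 64 per arm and 128 in total, with power 80.1%. Inflation gives 128 / 0.70 = 182.9, against the stated 182. The plan's figures therefore reproduce to within one patient.

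**Possible size.** The protocol states no rate of randomized, never-dosed leavers, so the rates below are assumptions. The last column supposes that these patients come on top of the 30% dropout: evaluable number = 0.70 × (182 − removed), with power from the same t-test.

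| Assumed rate | Removed from 182 | Set under 5.4 | Evaluable | Power |
|---|---|---|---|---|
| 0% | 0 | 182 | 127.4 | 80.0% |
| 1% | 2 | 180 | 126.0 | 79.5% |
| 2% | 4 | 178 | 124.6 | 79.1% |
| 5% | 9 | 173 | 121.1 | 77.9% |
| 10% | 18 | 164 | 114.8 | 75.7% |

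If these patients are instead counted among the 30%, planned power does not change. That is the natural reading, since someone who leaves without dosing is a dropout.

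**Effect on the primary model.** Section 9.5 substitutes no missing data in the primary analysis, and section 9.1.2 models change from baseline. A leaver with no post-baseline score supplies no change value, so including or excluding that patient leaves the treatment estimate essentially as it was. A leaver who attends the Early-Termination visit does have a post-baseline CNS-VS score, and the model is to use all timepoints. For that patient the choice between 5.4 and the other sections can affect the estimate.

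**The case against.** The strongest reply is that this is a narrow wording conflict with almost no numerical consequence. Much of that stands.

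- The window is short: baseline assessment, randomization and product supply all take place at Visit 2, so few patients should be randomized and never dosed.
- Treatment is double-blind, so leaving before any dose is unlikely to depend on the assigned arm.
- Several routes out leave nothing to collect. Section 5.4 bars contact after notice of withdrawal, lost patients cannot be reached, and study procedures are separately cancelled in pregnancy. Outcomes are given up mainly in undosed patients withdrawn for a medical condition, or who leave without withdrawing consent to outcome collection.
- The LOCF point is conditional. The protocol does not say whether a baseline value is carried forward when nothing follows it.

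Three stronger readings are tempting and are not supported. A reader might infer that 5.4 drops every randomized patient who took no dose; it applies only to those who also left the study. A reader might set the patients removed against the 127.4 expected evaluable and the 128 required, and infer a shortfall; that gap is rounding in the inflation step, and these leavers belong within the 30% allowance. A reader might infer material bias in the primary comparison; with no imputation, blinding and probably few patients, the documents do not show that.

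What the reply does not remove is that two current sections give opposite instructions for the same patient, and that 5.4 also contradicts the visit required by 4.1.

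**Conclusion.** The conflict is real and lies in current text. For a randomized patient who takes no dose and leaves, 9.7 requires inclusion in the primary set, 5.4 requires exclusion and no further follow-up, and 4.1 requires an Early-Termination visit. The consequences are an uncertain ITT count, a primary set that may be a modified ITT in all but name, a possible difference in the LOCF set, and the loss of some obtainable outcomes.

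The number affected cannot be derived from the protocol and is probably small. The effect on the primary estimate should be slight, and planned power is untouched if these patients fall within the dropout allowance. It should be corrected because the plan's own ITT definition forbids the exclusion, and because follow-up cancelled at the sites cannot be recovered later.

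**What to change.** Amend section 5.4 in three respects:

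1. Limit the exclusion from analysis to patients who were never randomized. For randomized patients who took no dose, limit it to the Safety population, as 9.7 already does.
2. State that randomized but undosed patients remain in ITT as 9.7 defines it, in their assigned arm.
3. Reconcile the cancellation of follow-up with the Early-Termination visit in 4.1, so that outcomes are collected unless consent is withdrawn or the patient cannot be contacted. The separate provision for pregnancy is not part of this point.

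If the sponsor does intend a randomized-and-dosed primary set, 9.7 and 9.1.2 should call it modified ITT and justify it, and the conflict with 4.1 would still need settling. Either course should be fixed before unblinding.

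The cost is a short amendment of a sentence or so and, at most, outcome visits for a few patients. The sample size does not change.

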## 5.5 Replacement of the Subjects

This study does not provide for the replacement of withdrawn study participants.

## **5.6 Follow-up of the Withdrawn Patients**

The subjects that were withdrawn from the study because of an AE/SAE will be followed until the AE/SAE is resolved or the patient is stabilized.

## **5.7 Strategies for Recruitment and Retention**

### **5.7.1 Recruitment**

It is anticipated that patients with mTBI will attend the participating clinical centers. Clinicians based within recruiting centers will be asked to identify potential participants from their patient lists, based on the eligibility criteria, and inform them about the study. Recruitment efforts will also include dissemination of information about this trial to other medical professionals/clinical centers.

### **5.7.2 Retainment**

As recommended by Corrigan et al (34) to minimize the risk of attrition multiple contact details for an alternative contact person will also be obtained if nominated by the participant. Participants will be asked as to their preferred method of contact.

A reminder phone-call or text will be sent before each appointment to help prevent missed appointments. All Investigators in the study will be trained on the importance of establishing rapport with study participants and how to convey why the study is important to participants. Participating subjects will be reminded of subsequent visits.

## 6 TREATMENT OF SUBJECTS

### 6.1 Treatment(s) to be Administered

The IP/Placebo will be supplied in kits. Each IP kit contains 3 sachets, 1 sachet contains 5 blisters, 1 blister contains 12 capsules.

In total, 182 subjects will be included in the study, therefore 7 IP kits are necessary for a treatment course. Maximum 10 sites are planned to participate in the study. Taking into account stratified block randomization by 2 binary stratification factors (4 strata per site totally) and possible variative block size, we assume that 12 kits per site will not be used due to possible imbalance within all strata and 12 kits per site should be reserved during the study for newly opened blocks. Thus, 1514 IP/Placebo kits are needed for study population, 1666 IP/Placebo kits needed for the study conduction (10% buffer to avoid transfer between sites).

#### 6.1.1 Investigational Product

Table 6.1. Description of IP.

| NeuroAiD II™ (MLC901)                               |                                                                                                                                                                                                                                                                                                                                                                                                                                                                                                                                                               |
|-----------------------------------------------------|---------------------------------------------------------------------------------------------------------------------------------------------------------------------------------------------------------------------------------------------------------------------------------------------------------------------------------------------------------------------------------------------------------------------------------------------------------------------------------------------------------------------------------------------------------------|
| Trade name:                                  | NeuroAiD II™                                                                                                                                                                                                                                                                                                                                                                                                                                                                                                                                                  |
| International Non-proprietary Name (INN):    | NeuroAiD II™ (MLC901)                                                                                                                                                                                                                                                                                                                                                                                                                                                                                                                                         |
| Manufacturer/Marketing Authorization Holder: | Moleac Pte Ltd,
[name]                                                                                                                                                                                                                                                                                                                                                                                                                                                                                           |
| Dosage form:                                 | Capsule 400 mg (size 0)                                                                                                                                                                                                                                                                                                                                                                                                                                                                                                                                       |
| Dosage:                                      | 
Recommended treatment is 2 capsules orally, 3 times a day (i.e. 6 capsules per day). Standard treatment is 12 weeks. MLC901 capsules could be:
 
 
- swallowed as such with water
 
- opened and drunk once powder has been diluted in a sufficient amount of water of room temperature*
 
 
*Clumping of the powder content may be observed due to the inherent nature of the powder extract. This does not indicate deterioration of quality if used within the specified shelf life.
 |
| Composition (per 1 capsule)                  | See Table 6.2.                                                                                                                                                                                                                                                                                                                                                                                                                                                                                                                                                |
| Appearance:                                  | The capsule cap is dark blue and capsule body is light blue in color. The capsule size is 0. The powder content is brown to dark brown colour and has some agglomerates.                                                                                                                                                                                                                                                                                                                                                                                      |
| Storage terms:                               | To be stored in a cool dry place not exceeding 30°C                                                                                                                                                                                                                                                                                                                                                                                                                                                                                                           |

|                               |                                                                                                                                                                                                                                                                                                                                                                                                                                                              |
|-------------------------------|--------------------------------------------------------------------------------------------------------------------------------------------------------------------------------------------------------------------------------------------------------------------------------------------------------------------------------------------------------------------------------------------------------------------------------------------------------------|
| Package and labelling: | Capsules are gelatin-free. They are made up of Hypromellose (hydroxypropyl methylcellulose HPMC) which is permitted as a food additive for human consumption in accordance with 21 CFR 172.874. The capsules are packed in blister made of PVDC/PE/PVC multilayer clear blister front and 25-micron aluminum backing with 12 capsules per strip. Every 5-blister strip (i.e. 60 capsules) is prepacked into an aluminum sachet before being placed in a box. |
|-------------------------------|--------------------------------------------------------------------------------------------------------------------------------------------------------------------------------------------------------------------------------------------------------------------------------------------------------------------------------------------------------------------------------------------------------------------------------------------------------------|

Table 6.2. Composition of MLC901.

| Active Ingredients           |                                                   |                    |                               |                                        |
|------------------------------|---------------------------------------------------|--------------------|-------------------------------|----------------------------------------|
|                              | Ingredients
(Latin names)                      | Parts Used         | Quantity* (mg)
per capsule | Equivalent extract
per capsule (mg) |
| 1                            | Radix Astragali                            | Dried root         | 800                           | 111.5                                  |
| 2                            | Radix et Rhizoma
Salviae miltiorrhizae | Dried root/rhizome | 160                           | 22.3                                   |
| 3                            | Radix
Paeoniae rubra                   | Dried root         | 160                           | 22.3                                   |
| 4                            | Rhizoma
chuanxiong                     | Dried rhizome      | 160                           | 22.3                                   |
| 5                            | Radix
Angelicae sinensis               | Dried root         | 160                           | 22.3                                   |
| 6                            | Flos Carthami                              | Dried flower       | 160                           | 22.3                                   |
| 7                            | Semen persica                              | Dried ripe seed    | 160                           | 22.3                                   |
| 8                            | Radix
polygalae                        | Dried root         | 160                           | 22.3                                   |
| 9                            | Rhizoma
Acori tatarinowii              | Dried rhizome      | 160                           | 22.3                                   |
| Excipients                   |                                                   |                    |                               |                                        |
|                              | Name                                              | Functions          | Quantity (mg) per
capsule  |                                        |
| 1                            | Dextrin                                           | Bulking agent      | 57                            |                                        |
| 2                            | Maltodextrin                                      | Bulking agent      | 51                            |                                        |
| 3                            | Magnesium stearate                                | Lubricant          | 2                             |                                        |
| Ingredients of Capsule Shell |                                                   |                    |                               |                                        |

|   | Name                           | Functions          | Quantity (mg) per capsule |
|---|--------------------------------|--------------------|---------------------------|
| 1 | Brilliant blue FCF-FD&C Blue 1 | Capsule colorant   | 0.0819                    |
| 2 | Titanium dioxide               | Capsule-opacifier  | 1.895                     |
| 3 | Hypromellose                   | Capsule- structure | 89.79                     |
| 4 | Water                          | Solvent            | 4.23                      |

